## Abstract

**Background:**

Recent studies have revealed a low measles vaccination (MV) rate in the Republic of Guinea-Bissau (West Africa) that has not increased in accordance with the increasing coverage of other vaccinations. Measles is the deadliest of all childhood rash/fever illnesses and spreads easily, implying that if the vaccination coverage is declining there is a significant risk of new measles outbreaks [27]. Meanwhile, mobile health (mHealth; the use of mobile phones for health interventions) has generated much enthusiasm, and shown potential in improving health service delivery in other contexts.

**Objective:**

The aim of this study is to evaluate the efficiency of mHealth as a tool for improving MV coverage while contributing to the mHealth evidence base.

**Methods:**

This study will take place at three health centers in different regions of Guinea-Bissau. Participants, defined as mothers of the children receiving the MV, will be enrolled when they arrive with their children at the health center to receive the Bacillus Calmette-Guérin vaccination, usually within one month of the child’s birth. Enrolment will continue until a study population of 990 children has been reached. The participants will be randomly assigned to a control arm or one of two intervention arms. Each of the three groups will have 330 participants, distributed equally between health centers. Participants in the first intervention arm will receive a scheduled short message service (SMS) text message reminding them of the MV. Participants in the second intervention arm will receive a voice call in addition to the SMS message, while the control arm will receive no interventions. The MV is scheduled to be administered at 9 months of age. Although the vaccine would still be effective after 12 months, local policy in Guinea-Bissau prevents children aged >12 months from receiving the vaccination, and thus the study will follow-up with participants after the children reach 12 months of age. Children who have not yet received the MV will be offered vaccination by the project group.

**Results:**

The study will analyze the efficiency of the intervention by determining its overall effect on MV coverage and timeliness when children reach 12 months of age. The main analysis will be stratified by intervention group, health center, level of education, ethnic group, and role of the person receiving the text messages (eg, mother, father, other family member). Secondary outcomes include the average number of health center visits (with intention to obtain the MV) required before successful administration.

**Conclusions:**

Despite the rapid proliferation of mHealth projects, only a small number have been evaluated in terms of direct links to health outcomes. This gap in knowledge requires solid evidence on which policy-makers can base decisions. This study aims to produce significant knowledge about mHealth implementation within a Sub-Saharan context while creating data-supported evidence.

**Trial Registration:**

Clinicaltrials.gov: NCT02662595; https://clinicaltrials.gov/ct2/show/NCT02662595 (Archived by WebCite at http://www.webcitation.org/6jH8YiSjY)

## Introduction

### Background

The use of mobile phones as a tool for health interventions (mHealth) has shown significant potential worldwide, and has been used in low income settings. The benefits of such interventions include low start-up costs [1] and the possibility of reaching a great number of people. According to recent reports [2,3], a number of mHealth initiatives have already been conducted around the world. Despite these advances, mHealth has untapped potential, especially in the African region, where the number of such initiatives is the lowest in the world [3]. Although the rapid proliferation of mHealth projects has generated enthusiasm [4], more evidence establishing their efficacy and effectiveness is needed [3,5,6].

Current studies from the International Network for the Demographic Evaluation of Populations and Their Health (INDEPTH) and the Global Alliance for Vaccines and Immunization (GAVI) reveal a low measles vaccination (MV) rate in Guinea-Bissau that has not increased in accordance with the increasing coverage of other vaccinations. In 2014 the United Nations International Children's Emergency Fund (UNICEF) estimated that MV coverage among children 12-23 months of age in Guinea-Bissau was 64% [7], a number that has steadily decreased since 2004 [8].

Meanwhile, other studies have shown that mHealth interventions can be efficient in increasing awareness and demand for health services [9-14]. An important prerequisite for mHealth projects to be successful is access to mobile phones, which has grown rapidly in many developing countries. According to the World Development Indicators provided by The World Bank, it was estimated that in 2013 there were 74 cellular subscriptions per 100 people in Guinea-Bissau (compared to 45 in 2011 and 63 in 2012) [15].

Measles is the deadliest of all childhood rash/fever illnesses and spreads easily, implying that if the MV coverage is declining [16] there is a significant risk of new measles outbreaks [17]. Recent reports from World Health Organization conclude that increased activities are needed to resume progress towards the 2015 Millennium Development Goals of measles control and elimination [18,19]. In addition, recent studies have lead the Strategic Advisory Group of Experts on Immunization to suggest that MV is associated with possible beneficial effects on all-cause mortality [20]. Interventions that enhance the timeliness and coverage of MV are therefore likely to have a great beneficial impact on child health. Thus, we suggest an mHealth intervention to increase MV coverage by sending vaccination reminders by short message service (SMS) texts to mothers before their child’s scheduled MV. While this intervention aims at increasing awareness amongst mothers, it also presents potential benefits regarding the supply of MVs. Current policies in Guinea-Bissau require a minimum number of children to be present before a vial of vaccine can be opened, and since the health centers typically only administer vaccinations one or two days per week, mothers will often the be sent home and told to return a different day. This intervention has the potential to coordinate the vaccination visits and help ensure that enough children are present for the health centers to open a vial of vaccines on a given day, and ensure that mothers arrive on the correct day at the health centers.

Studies from the INDEPTH Network and GAVI have demonstrated that rural regions have particularly low MV coverage, so this intervention will focus on the rural regions of Tombali, Gabu, and Cacheu in the Southern, Eastern, and Northern Guinea-Bissau, respectively.

### Objectives

The primary objective of this intervention is to enable a beneficial impact on child health by improving timeliness and coverage of MVs using simple and cost-efficient methods. Specifically, the study aims to investigate whether a mobile phone targeted reminder system can be used in the context of rural Guinea-Bissau, and what effect this intervention can be expected to have, as well as potential obstacles and barriers to implementation.

## Methods

### Trial Design

This study is designed as a multi-site, three arm, parallel randomized controlled trial (RCT). Participants will be randomized to either one of two intervention arms (one receiving an SMS reminder, the other receiving the SMS reminder and an additional voice call) or a control arm (no intervention) with a 1:1:1 allocation ratio (Figure 1).

**Figure 1 figure1:**
[figure not shown]
Study flow.

### Informed Consent Forms

Informed consent will be obtained for all study participants before enrollment. The study will be described to the potential participants by trained study workers at the health centers. The project description will be explained in the preferred language of either Portuguese or Creole. After the project has been explained, the potential participant will be asked a number of questions related to the project to ensure adequate understanding, and informed consent forms will be signed.

### Randomization and Blinding

Three randomization sequences (one per health center) were generated using a software algorithm. The randomization sequences are only accessible for the central project group, and will be used when the central project assistant is adding study participants to the scheduling system and delivering phone messages. Participant allocation is concealed to the study assistants at the health facilities, and will only be revealed during the follow-up interview when, and if, the participants come to the health facility to receive MVs.

### Setting and Participants

Study participants, defined as mothers of the children receiving the MV, will be enrolled at one of three selected health facilities when their children receive their first vaccination, usually the Bacillus Calmette-Guérin vaccine, which is administered shortly after birth. The study will be explained to the mothers by the health workers in the local language (Portuguese Creole), and pending their informed consent, the mothers will be enrolled in the study. Enrollment is completed by the health worker, who will take note of the participant’s phone number(s), date of birth, and the baby’s name. A sticker with a unique study identification number will be placed on the child’s vaccination card to indicate that this child is participating in the study.

The inclusion criteria for enrollment in the study are that the participant has access to a cell phone (either her own phone or the phone of a household member or community contact) and that she lives in the uptake area of the health center.

A study assistant will collect information regarding the participant, including age, ethnic group/primary language, and level of education. This information will be entered into a digital questionnaire using an Android device. The data will be successively transferred to a central information technology (IT) system, where a central study assistant will randomize participants and enter the data into the system responsible for scheduling and sending SMS messages, and creating call-lists for the participants scheduled to receive verbal messages.

The enrollment period for this study component will continue until a study population of 990 children (see sample size calculation below) has been reached (total enrollment time is estimated to be approximately 6 months). We will follow up after children reach 12 months of age, since MVs are scheduled to be administered at 9 months of age, and local policy in Guinea-Bissau prevents children aged >12 months from receiving the MV. Thus, this component of the intervention is estimated to last no longer than 18 months.

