### Intervention

The intervention being evaluated is a cell phone reminder and coordination system, which seeks to coordinate potential recipients of MV with MV opportunities (ie, days in which MV is administered either at their local health center, or at a relevant outreach day). Participants allocated to intervention groups will receive two SMS text reminders in the local language of Portuguese Creole. The first message will be delivered three days before the suitable MV opportunity, and the second will be sent one day before. If the participant is allocated to also receive a phone call, a project worker will call the supplied phone number two days before the MV opportunity.

SMS messages are *active* in the cell phone network for 24 hours, after which the delivery attempt will be considered failed. If the delivery attempt of a first message fails (ie, three days before MV opportunity), the message will be redelivered. If delivery of the second message fails (ie, one day before MV opportunity), it will not be redelivered due to time rendering it irrelevant. If a phone call fails it will be reattempted two times: once on the same day, and a final attempt on the day before MV opportunity. We will register all failed message delivery attempts and account for these in the subsequent analysis.

If several phone numbers are supplied, SMS texts will be sent to all phone numbers. Voice calls will made to one number, and if the call to the first number is not successful, the second number will be attempted, and so on. Voice calls, like the SMS texts, will be made in the Creole language.

If a study participant does not arrive at the MV opportunity, or if the MV opportunity is cancelled or unavailable for any reason, the study participant will receive a new set of messages/voice calls at the next relevant MV opportunity, assuming the child is still eligible (ie, child is 9-12 months of age). The new set of messages will be delivered regardless of whether earlier delivery attempts for the participant failed.

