### Safety & Ethics

#### Ethical Considerations

One of the key challenges in relation to mHealth is the issue of privacy and data security [23], especially when potentially stigmatizing diseases or substance abuse could be disclosed if family members or others see the text messages, or gain access to the phone used for the intervention [24]. This issue becomes all the more relevant since we have chosen to include mothers, some of whom do not have their own phones, but only have access to shared phones. However, it is our judgment that vaccination reminders do not represent any risk of unwanted disclosure. In addition, a recent study from Argentina concluded that 96% of the study participants (pregnant women attending antenatal care) responded that they would like to receive text messages and phone calls [25]. We have chosen to include participants who do not have their own private phones in an attempt to avoid adding further to the *digital divide* (ie, social inequality due to lack of access to and/or knowledge of information and communication technology).

Another ethical consideration is how to embrace illiteracy/multiple spoken languages without adding to cultural divides or discrimination against certain population segments or ethnic groups. Culture-specific wording of messages is also important, in order to avoid unintended negative effects [26]. At the time of enrollment, trained health workers will describe the study in detail to the potential participants, and assess their understanding in order to obtain their informed consent. All information will be available in Creole (the primary spoken language of Bissau).

To avoid sending SMS reminders to participants who have died or moved out of the study area, or those whose children have died or received the vaccine ahead of schedule, follow-up will be done to the extent possible at the health facilities. It is likely that some of these events will go unnoticed, potentially resulting in inappropriate messages being sent. This problem does not differ from current practices of the Health and Demographic Surveillance System routines, in which families are occasionally asked about deceased members of the household. The possibility of receiving a message regarding a deceased child will furthermore be explained during the informed consent phase.

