#### Sample Size Calculations

Current statistics indicate MV coverage of approximately 75% at 12 months of age in the rural areas of Guinea-Bissau. Drawing on experiences from other studies implementing SMS reminders [13], we aim for an increase in MV coverage of 10 percentage points. Using a significance level of 5% and 80% power, and a hypothesized increased MV coverage to at least 85% in each of the intervention arms (compared to the control arm), a total of 810 children are needed (270 in each arm). Adjusting for expected loss-to-follow-up between 15-20% (eg, outmigration, death, children being vaccinated elsewhere), which is comparable to other mHealth studies [27], we plan to enroll 990 study participants (330 in each arm).

The current median age of MVs given before 12 months of age in rural Guinea-Bissau is approximately 295 days of age [7]. The age distribution is fairly normal, and in the following power calculation we have used a normal approximation: with 270 children in each arm and an MV coverage of at least 75%, we are able to detect a change of 7 days in median age (using a significance level of 5% and 80% power).

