#### Statistical Analysis

The main outcome of MV coverage at 12 months of age (366 days of age) will be calculated as percent who received MV at the health centers, among all children enrolled. Furthermore, coverage will also be calculated based on follow-up interviews when children reach 13 months of age, among study participants whose children did not receive the MV at the health centers. The coverage (percentages) will be compared using Mantel-Haenszel statistics stratified for health center for each of the intervention groups (SMS and voice calls) compared with the control group. The secondary outcome B (Textbox 1) of timeliness of MVs will compare age distributions between vaccinated children, among all children having received MVs before 12 months of age (366 days), using linear regression adjusted for health center. A statistical significance level of 5% will be used. A subanalysis will stratify for study participants having their own private mobile phone versus those using the phone number of another community member. Due to the groups being randomized, we do not expect baseline imbalances. In the case that such trends do occur, we will be unable to rule out other imbalances or unmeasured confounders. The main outcome will therefore be the crude estimate. However, we will investigate the impact of adjusting for unbalanced background factors in sensitivity analyses. The study will be conducted and reported in accordance with Consolidated Standards of Reporting Trials guidelines [28].

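### Children appear to be randomized 8-9 months before any reminder can act and all stay in the primary denominator; this dilutes the effect without biasing it, and randomizing later would recover some power cheaply

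*Protocol article*

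**What the plan says.** Under Setting and Participants, mothers are enrolled at the child's first vaccination, usually BCG shortly after birth; the Abstract puts this at usually within one month of birth. The inclusion criteria are phone access and residence in the uptake area, both judged at that visit. Enrolment data then pass to a central system, "where a central study assistant will randomize participants and enter the data into the system responsible for scheduling and sending SMS messages". Randomization and Blinding adds that the sequences are used when participants are added to the scheduling system and messages are delivered. Neither section gives a date or a child's age for randomization.

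Reminders are tied to measles vaccination (MV) opportunities, and MV is scheduled at 9 months. Under Intervention, a further set of reminders follows a missed opportunity "assuming the child is still eligible (ie, child is 9-12 months of age").

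Ethical Considerations accepts that participants or children may die or move, and that children may be vaccinated early. It says that "follow-up will be done to the extent possible at the health facilities" and that some of these events will probably be missed. It treats this only as a risk of inappropriate messages.

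Sample Size Calculations starts from 270 per arm and reaches 330 per arm: "Adjusting for expected loss-to-follow-up between 15-20% (eg, outmigration, death, children being vaccinated elsewhere"). Statistical Analysis defines the main outcome as the percentage vaccinated at the health centers by 366 days, with all enrolled children in the denominator.

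**The concern.** If allocation follows enrolment closely, the arms are treated identically for some 8-9 months. A child who dies or leaves the area in that time is already in an arm, cannot respond to a reminder, and counts as unvaccinated. A child vaccinated early at the center counts as vaccinated whatever the arm. Both kinds pull the coverage rates together.

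What is at stake is the size of the detectable difference and hence power. The dilution is expected to be equal in all arms, so it does not favor any of them. It is also partly avoidable: nothing in the design needs an allocation before the first reminder is due, and a child left out before allocation cannot be left out because of its arm.

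**Working it through.** **Inputs.** From Sample Size Calculations: "Using a significance level of 5% and 80% power"; control coverage ("Current statistics indicate MV coverage of approximately 75% at 12 months of age in the rural areas of Guinea-Bissau"); "hypothesized increased MV coverage to at least 85% in each of the intervention arms"; 270 per arm before loss and 330 after; loss of 15-20%. Sidedness is not stated (Statistical Analysis says only "A statistical significance level of 5% will be used"). Two-sided is assumed, because one-sided gives 197 per arm and does not match 270.

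**1. The plan's own figure.** The two-proportion formula with pooled variance, 75% versus 85%, two-sided 5%, 80% power, gives 250 per arm, or 270 with continuity correction. The stated 270 is reproduced. 270/(1 − 0.18) = 329.3, so 330 per arm corresponds to about 18% loss.

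**2. When allocation happens.** No date is given. The 330 per arm already includes the children expected to die, move or be vaccinated elsewhere, so those losses occur inside the arms. Allocation before the losses is therefore the likelier reading, but it is an inference.

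**3. Power with the denominator as written.** Let L be the loss, scored as unvaccinated. The rates become 0.75(1 − L) and 0.85(1 − L), with n = 330 per arm. Power = Φ[(d − 1.96·se0)/se1], where d is the difference in rates, se0 = √(2·p̄(1 − p̄)/n) and se1 = √((p1(1 − p1) + p2(1 − p2))/n), without continuity correction.

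For L = 0.15: p1 = 0.6375, p2 = 0.7225, d = 0.085, p̄ = 0.68, se0 = 0.0363, se1 = 0.0362. Power = Φ(0.382) = 0.649.

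| Loss | Rates | Difference | Power at 330 per arm |
|---|---|---|---|
| 15% | 63.8% v 72.3% | 8.5 points | 65% |
| 18% | 61.5% v 69.7% | 8.2 points | 60% |
| 20% | 60.0% v 68.0% | 8.0 points | 57% |

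**4. How much of this is the denominator.** By the same formula, if lost children left the denominator as the inflation step presumes, 330 × 0.85 = 280 or 330 × 0.80 = 264 per arm at 75% versus 85% gives 84% or 82%. The fall from 84% to 65%, or from 82% to 57%, is therefore the mismatch between the two sections, with the timing of randomization unchanged.

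**5. What later randomization recovers.** Let s be the share of the loss that falls before 9 months and k the share of those early losses known at that point. The documents give neither. The fraction L·s·k is left out before allocation, so n = 330(1 − Lsk) and both rates are multiplied by (1 − L)/(1 − Lsk).

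Example, L = 0.15, s = k = 0.5: Lsk = 0.0375, n = 317.6, factor = 0.85/0.9625 = 0.883, rates 66.2% v 75.1%, power 69%.

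| s (early share) | k (known) | Power, 15% loss | Power, 20% loss |
|---|---|---|---|
| as written | – | 65% | 57% |
| 1/4 | 1/4 | 66% | 58% |
| 1/4 | all | 69% | 61% |
| 1/2 | 1/2 | 69% | 61% |
| 1/2 | all | 73% | 67% |
| 3/4 | 1/4 | 68% | 60% |
| 3/4 | 1/2 | 71% | 64% |
| 3/4 | all | 78% | 74% |

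Power rises in every row although fewer children are randomized. No row reaches 80%.

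**6. Early vaccination at the center.** Its frequency is not given. An assumed 2-10%, taken alone, lowers power at 330 per arm from 90% to 89-85%. It is the weakest source of dilution.

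**The case against.** The strongest objection is that the shortfall is mainly not about timing. Step 4 shows that it arises from the denominator, and removing that mismatch with timing unchanged would give 82-84%. This stands.

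The larger gains also rest on weak ground. Vaccination elsewhere is one of the named causes of loss, and since MV is due at 9 months it falls mostly after the proposed randomization. A three-quarters early share is therefore probably too high. Full knowledge of early losses is unrealistic, because the protocol itself expects some events to go unnoticed. This stands too, and is why the gain is given as a range.

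Keeping everyone from registration is also a legitimate choice: it estimates the effect of a system that registers mothers at the first vaccination. Later randomization narrows the population somewhat.

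A reader might infer more than the documents support:
- That the protocol states randomization at the first vaccination. It gives no date, and the Randomization and Blinding wording leaves a later point possible.
- That the comparison is biased. Dilution from events before any reminder is expected to be the same in all arms.
- That deaths and moves come to light mainly through calls in the voice arm. Follow-Up plans a 13-month phone interview, in every arm, for all participants not registered as vaccinated, and it records vaccination elsewhere, moves and deaths.
- That children enrolled too late to meet the 366-day outcome are a material problem. No age ceiling is written, but enrolment is usually within a month of birth, so such cases should be rare.

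**Conclusion.** The point holds as an efficiency matter. Randomization very probably precedes the first possible reminder by about 8-9 months, and the primary denominator keeps every child enrolled. Power at 330 per arm is then about 65% at 15% loss and 57% at 20%, against the planned 80%.

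This assumes that all of the stated loss scores as unvaccinated and that 75% and 85% describe children who remain reachable. If those rates already describe all enrolled children, power is about 90%, but the inflation for loss would then be unnecessary. The 13-month interview coverage can recover children vaccinated elsewhere, but not deaths or families who cannot be reached, and it is an additional calculation.

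The part attributable to timing is modest. With a quarter to three quarters of losses before 9 months and a quarter to all of them known, power becomes 66-78% (15% loss) or 58-74% (20% loss). In the middle case the gain is about 4 points. It would be tempting to say that later randomization solves the power problem, but even its best case stays below 80%. It is a cheap improvement alongside the separate correction of the loss adjustment.

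**What to change.** Keep consent and enrolment at the first vaccination. Apply the central randomization sequence just before the child's first scheduled reminder, and only to children who are not already known from facility records to have died, moved out of the uptake area or received MV, and who are still below the first-reminder age. Define the primary denominator as all children randomized, and state the timing of randomization explicitly. If the authors already intend a late allocation, stating it is enough for the timing part.

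Reconcile the loss inflation in Sample Size Calculations with the denominator in Statistical Analysis as a separate correction.

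The cost is a wording change and a later trigger in the central scheduling system; allocation is already central and facility follow-up of these events is already planned. No extra enrolment is needed to obtain the gains shown. The downside is that fewer than 990 children are randomized, and the conclusion applies to children still believed eligible at about 9 months. Events unknown to the facility remain in the comparison, as now.
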